## Abstract

**Background:**

It is well known that obstructive jaundice could affect the pharmacodynamics of some anesthetics, and the sensitivity of some anesthetics would increase among icteric patients. Remimazolam is a new ultra-short-acting intravenous benzodiazepine sedative/anesthetic, which is a high-selective and affinity ligand for the benzodiazepine site on the GABAA receptor. However, no study has reported the pharmacodynamics of remimazolam in patients with obstructive jaundice. We hypothesize that obstructive jaundice affects the pharmacodynamics of remimazolam, and the sensitivity of remimazolam increases among icteric patients.

**Methods/design:**

The study will be performed as a prospective, controlled, multicenter trial. The study design is a comparison of remimazolam requirements to reach a bispectral index of 50 in patients with obstructive jaundice versus non-jaundiced patients with chronic cholecystitisor intrahepatic bile duct stones. Remimazolam was infused at 6 mg/kg/h until this endpoint was reached.

**Discussion:**

Remimazolam could be suitable for anesthesia of patients with obstructive jaundice, because remimazolam is not biotransformed in the liver. Hyperbilirubinemia has been well-described to have toxic effects on the brain, which causes the increasing of sensitivity to some anesthetics, such as desflurane, isoflurane, and etomidate. Furthermore, remimazolam and etomidate have the same mechanism of action when exerting an anesthetic effect. We aim to demonstrate that obstructive jaundice affects the pharmacodynamics of remimazolam, and the dose of remimazolam when administered to patients with obstructive jaundice should be modified.

**Trial registration:**

Chinese Clinical Trial Registry ChiCTR2100043585. Registered on 23 February 2021

## Background

Obstructive jaundice is defined as the retention of bile components and bile after intrahepatic or extrahepatic bile duct obstruction [1]. Patients with obstructive jaundice are prone to acute renal failure, hypotensive shock, sepsis, and multiple organ dysfunction in the perioperative period [2, 3].

Remimazolam is a new, fast-onset, and ultra-short-acting intravenous sedative/anesthetic [4], which is a high-selective and affinity ligand for the benzodiazepine site on the GABAA receptor [5] and rapidly metabolized by tissue esterases to an inactive metabolite [6, 7]. In recent years, there has been a growing interest in the use of remimazolam in general anesthesia and procedural sedation [4]. It is well known that obstructive jaundice could affect the pharmacodynamics of some anesthetics, and the sensitivity of some anesthetics would increase among icteric patients. We have found that patients with obstructive jaundice are more sensitive to etomidate [8]. In the meanwhile, remimazolam and etomidate have the same mechanism of action when exerting an anesthetic effect, which suggests that patients with obstructive jaundice may also be more sensitive to remimazolam.

## Methods/design

### Study settings

The study is designed as a prospective, controlled, multicenter trial. It is registered in the Chinese Clinical Trial Registry (ChiCTR2100043585. Date of registration: February 23, 2021). This study mainly aims to investigate whether obstructive jaundice affects the pharmacodynamics of remimazolam and whether the sensitivity of remimazolam increases among icteric patients. It is reported following the SPIRIT reporting guidelines [9]. The sponsor of this trial is the Department of Anesthesiology, Shidong Hospital of Shanghai, University of Shanghai for Science and Technology. The sponsor is responsible for the design, collection, management, analysis, and interpretation of the data; writing; and the decision to submit the report for publication. The study is supported by the Yangpu District Good-Doctor Program funding and The Science and Technology Commission and Health Committee of Yangpu District, Shanghai (YPM202105). Figure 1 shows the SPIRIT checklist that we follow in this report.

**Fig. 1 Fig1:**
[figure not shown]
Schedule of enrollment, intervention, and assessment according to the Standard Protocol Items: Recommendations for Interventional Trials (SPIRIT) statement

### Participants

#### Number of patients needed

We plan to divide the patients into the obstructive jaundice group (total bilirubin (TBL) value > 17.1 μmol/L) and the control group (TBL < 17.1 μmol/L) based on their diagnosis and TBL value. The primary endpoint is the difference in the requirement of remimazolam.

The group sample size was calculated based on the differences in remimazolam requirement to reach BIS value ≤ 50 longer than 5 s in our previous study, in which the mean remimazolam requirement was 0.13 ± 0.04 mg/kg (*n* = 6) in the obstructive jaundice group and 0.16 ± 0.04 mg/kg (*n* = 6) in the non-obstructive jaundice group, The following formula: *n* = 15.7/ES^2^ + 1, where ES = effect size = (difference between the groups)/(mean of the SD between the groups), with *α* = 0.05 and power = 0.8, was used to determine that the study would be adequately powered with *n* = 29 per group. Considering a dropout rate of 10%, the estimated sample size will be at least 32 patients per group; thus, a total of 64 patients will be needed.

#### Eligibility

The study takes place at three centers: the Department of Anesthesiology, Shidong Hospital of Shanghai, University of Shanghai for Science and Technology; Department of Anesthesiology, Eastern Hepatobiliary Surgery Hospital, Second Military Medical University; and Department of Anesthesiology, Chongqing University Cancer Hospital beginning March 2021 to March 2022. Eligible patients for participation in this clinical trial are 32 patients with obstructive jaundice (serum TBL > 17.1 μmol/L) secondary to neoplasm of the bile duct or the head of the pancreas and 32 non-jaundiced patient controls with chronic cholecystitisor intrahepatic bile duct stones. All patients enrolled in this clinical trial are aged 18 to 75 years, American Society of Anesthesiologists (ASA) grades II to III, and given written informed consent, who are scheduled to undertake surgery.

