### Allocation and allocation concealment

Patients are allocated to the obstructive jaundice group or the control group based on the TBL values after they sign the informed consent form. Because obstructive jaundice is easy to distinguish from the appearance of skin color, it is difficult to double-blind. However, the anesthesiologist assistant is blind to the grouping or induction method but only records the data through a local area network (LAN) in the next room.

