In our other research, it was shown that the etomidate requirement was significantly decreased in patients with obstructive jaundice, and there was a significant negative correlation between serum total bilirubin and etomidate requirement [8]. Etomidate is a pure hypnotic GABA agonist [31–33]. Shi et al. demonstrated that bilirubin potentiates inhibitory synaptic transmission in the lateral superior olive neurons of rats, and the potentiation of depolarizing GABA/glycinergic transmission by bilirubin could underlie bilirubin excitotoxicity [34, 35].

It just so happens that the remimazolam we are discussing is also a high-affinity and selective ligand for the benzodiazepine site on the GABAA receptor. Moreover, remimazolam does not show selectivity between GABAA receptor subtypes [5]. In other words, remimazolam and etomidate have the same mechanism of action when exerting an anesthetic effect. Patients with obstructive jaundice are more sensitive to etomidate [8], which suggests that patients with obstructive jaundice may also be more sensitive to remimazolam.

In conclusion, the toxic effects of hyperbilirubinemia on the central nervous system, such as histologic evidence of neurologic damage, altered neurotransmission in the brain, presynaptic neurodegeneration at the central glutamatergic synapses, and impairment of the release and uptake of the neurotransmitter glutamate, may induce the increased sensitivity to anesthetics and the reduction of anesthetic requirements.

The aim of our trial is to show that obstructive jaundice affects the pharmacodynamics of remimazolam, and the sensitivity of remimazolam increases among icteric patients; thereby, anesthesiologists caring for patients with obstructive jaundice should be alert to the interaction of bilirubin and remimazolam sensitivity.

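### Jaundice status coincides with neoplastic versus benign disease in every patient, so the primary group comparison cannot by itself be attributed to jaundice or bilirubin

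*Protocol article*

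**What the plan says.** The Eligibility section defines the two groups by disease as well as by TBL. It takes 32 patients with TBL above 17.1 μmol/L whose obstructive jaundice is "secondary to neoplasm of the bile duct or the head of the pancreas and 32 non-jaundiced patient controls with chronic cholecystitisor" or stones of the intrahepatic ducts. The Methods/design paragraph of the abstract gives the same control definition ("patients with obstructive jaundice versus non-jaundiced patients with chronic cholecystitisor intrahepatic bile duct stones"), and the section on the number of patients needed says that patients are divided "based on their diagnosis and TBL value". The allocation section mentions TBL alone: "Patients are allocated to the obstructive jaundice group or the control group based on the TBL values after they sign the informed consent form". There is no randomisation.

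The Statistical analysis section plans a t test or rank-sum test between the groups. It also plans a multiple linear regression of remimazolam dose on TBL, TBA, ALB, AST and ALT. It does not say whether the regression pools the two groups, and it lists no term for group or diagnosis.

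The intended conclusion concerns jaundice itself. The Discussion paragraph of the abstract says "We aim to demonstrate that obstructive jaundice affects the pharmacodynamics of remimazolam" and goes on to say that dosing in these patients should change. Study settings states the same question as an investigation. The main Discussion closes by saying that "anesthesiologists caring for patients with obstructive jaundice should be alert to the interaction of bilirubin and remimazolam sensitivity".

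**The concern.** The exposure of interest is jaundice, but the patients who have it differ from the controls in a second respect that the eligibility rules fix completely: they have a tumour and the controls do not. Anything about neoplastic disease that alters hypnotic requirement enters the group difference in full and would be reported as an effect of jaundice. Measured covariates such as albumin may absorb part of it, but no covariate can stand for the diagnosis, because the diagnosis and the group are the same variable.

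At stake is the interpretation of the primary endpoint. A real difference in requirement would still be a valid description of these two kinds of patient. It would not show that bilirubin or biliary obstruction is the cause, and it would not carry over to jaundice from benign obstruction. The article does not acknowledge this limit.

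**Working it through.** **1. The plan's own figure.** Inputs from the section on the number of patients needed: means 0.13 and 0.16 mg/kg, SD 0.04 in both groups, alpha 0.05, power 0.80.

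- ES = (0.16 − 0.13)/0.04 = 0.75
- n = 15.7/0.75² + 1 = 28.9, so 29 per group, as stated. Two-sample t power at 29 per group is 0.801.
- The planned enrolment is 32 per group, 64 in total. The sample size is not the issue here.

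**2. Who can be in each cell under the eligibility rules.**

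| | Neoplasm | Cholecystitis or stones |
|---|---|---|
| Jaundiced | 32 | 0 |
| Not jaundiced | 0 | 32 |

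Let J indicate jaundice and N indicate neoplasm. Then J = N for every patient, and

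E(dose) = a + b_J·J + b_N·N = a + (b_J + b_N)·J.

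The matrix [1, J, N] for 64 patients has rank 2, not 3. The group difference estimates b_J + b_N, and b_J alone is not estimable at any sample size.

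**3. Does the TBL regression separate them?** Consider first dose on TBL alone, pooled over both groups. With W and B the within-group and between-group sums of squares of TBL,

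slope_pooled = (W·slope_within + B·slope_between)/(W + B),

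where slope_between = (difference in mean dose)/(difference in mean TBL). The numerator of slope_between contains b_N, so the pooled slope carries the same confounding. Because the groups are defined by TBL above or below 17.1 μmol/L, B cannot be zero. The other listed covariates (TBA, ALB, AST, ALT) do not include the diagnosis, so adding them does not remove the problem.

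If the model is fitted in the jaundice group only, or includes a group term, the between-group part drops out. N is constant within each group, so the TBL slope is then estimated with neoplasm status held fixed.

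**4. Precision of the within-group gradient.** By the Fisher approximation, the simple correlation detectable with two-sided alpha 0.05 and power 0.80 satisfies atanh(r) = (1.96 + 0.84)/√(n − 3).

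- n = 32: 2.80/√29 = 0.520, r = 0.48
- n = 29: 2.80/√26 = 0.549, r = 0.50

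Only a fairly strong gradient would be detected reliably. Four further covariates would generally reduce precision.

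**5. Illustration of what a neoplasm effect would do.** The shifts are assumptions. Suppose b_J = 0, SD 0.04 and 29 per group, so SE = 0.04·√(2/29) = 0.0105 mg/kg. The probability of a significant two-sided t test is:

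| Assumed neoplasm shift (mg/kg) | P(significant) |
|---|---|
| 0.005 | 0.08 |
| 0.01 | 0.15 |
| 0.015 | 0.29 |
| 0.02 | 0.46 |
| 0.03 | 0.80 |

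The last row is simply the planning effect under another label.

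**6. Cost of adding non-jaundiced neoplasm controls.** Suppose k of the 32 controls have a neoplasm, the model has a neoplasm term, and no jaundiced patients with benign disease are added. The jaundice effect then comes only from the 32 jaundiced patients versus the k neoplasm controls: SE = 0.04·√(1/32 + 1/k).

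| Comparison | SE (mg/kg) | Power at 0.03 mg/kg |
|---|---|---|
| Planned 32 v 32, no neoplasm term | 0.0100 | 0.84 |
| k = 16 | 0.0122 | 0.67 |
| k = 8 | 0.0158 | 0.46 |
| k = 4 | 0.0212 | 0.29 |

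These figures are before dropout.

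**The case against.** The strongest reply is that the plan does not rest on the group test alone. It regresses dose on continuous TBL, and TBL varies among jaundiced patients who all have a neoplasm. A reader might infer from the eligibility rules that nothing about bilirubin can be learned from this trial. The documents do not support that: a within-group gradient is estimable from data the trial already collects. What remains open is that the article does not say the regression is within group. Even a within-group gradient would be partial evidence, because TBL may track tumour extent.

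A second reply is that the design already closes some routes by which tumour disease could act. Patients on analgesic or neuromodulating drugs are excluded, as are those with weight beyond 20% of ideal, with ASA I, IV or V, and with cardiac, pulmonary, renal or metabolic disease. The endpoint is reached before sufentanil, intubation and surgery, so the type of operation has no evident route to the measured dose. Albumin is a planned covariate. All this stands, and it makes a large neoplasm effect less likely, but it does not break the coincidence of tumour and jaundice.

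Third, the probabilities in step 5 are ordinary power values at assumed shifts. A reader might take them as the trial's false-positive rate. They are not: no document gives a neoplasm effect, and none is shown to exist.

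Finally, a reader might see a contradiction between the allocation section, which names TBL only, and the eligibility rules. It is a weak one. The abstract, the sample-size section and the Eligibility section all bring in the diagnosis, so non-jaundiced patients with a neoplasm do not enter the control group.

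**Conclusion.** The point holds for the primary comparison. Under the stated eligibility rules, the t or rank-sum contrast estimates the joint effect of jaundice and neoplastic disease. It cannot by itself support the attribution to obstructive jaundice or bilirubin made in the abstract, posed in Study settings and repeated in the Discussion. This follows from the group definitions alone and needs no assumed number. A fuller analysis plan could not undo it for the group contrast, because eligibility creates it.

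The point does not extend to every analysis of bilirubin. The TBL regression can contribute if it is within group; pooled, it carries the same confounding. Nor do the documents show that a neoplasm effect is present. Its size is unknown, and the 0.01 to 0.03 mg/kg shifts (significant with probability 0.15 to 0.80) only show that a shift of that order would matter. The article's word is neoplasm, so the coincidence is with neoplastic disease and should not be narrowed to malignancy.

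**What to change.** Two changes are enough.

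1. In the abstract's Discussion paragraph, Study settings and the closing part of the main Discussion, state the aim and conclusion as a comparison of obstructive jaundice due to neoplasm of the bile duct or pancreatic head with benign, non-jaundiced biliary disease. Acknowledge that the group difference may include an effect of the neoplasm.
2. In Statistical analysis, specify that the regression of remimazolam requirement on TBL is fitted within the jaundice group, or on all patients with a group term. Attribute an effect to bilirubin only if that within-group gradient supports it, and note that TBL may still follow tumour extent.

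Both use data already being collected. The cost is a narrower headline claim and a gradient estimated from about 32 patients, so a failure to find one should not be read as evidence against a bilirubin effect.

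Admitting non-jaundiced patients with the same neoplasms as controls would address the design directly, but it is optional and not cheap. It needs a stated minimum number, since a rule that merely permits such controls could yield none. With 16 of them and a neoplasm term, power at 0.03 mg/kg falls from about 0.84 to 0.67 at the same total. Recruitment began on 1 March 2021, so a change now would also mix two control populations.

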#### Exclusion criteria

Patients are excluded if the following criteria appear in their medical history:
Age range < 18 years or > 75 yearsASA physical status I, IV, or VWeight beyond ± 20% of idealAllergic reaction to the planned medicationHistory of psychological problems or psychiatric diseaseUsing any form of analgesic or neuromodulating medicationsKnown or suspected cardiac, pulmonary, renal, or metabolic disease

The schedule of enrollment, intervention, and assessment is reported according to the SPIRIT statement (Fig. 1).

The number of excluded patients and the reasons for their exclusion will be reported according to the SPIRIT statement.

#### Consent

Written consent was obtained from all patients. The patient’s history and current health status are screened during the standard anesthesia evaluation before the surgery. The investigators use anesthesia pre-assessment sheets to screen patients for inclusion and exclusion criteria. Inclusion will not be finalized until the patient signs the informed consent on the day of surgery.

If patients refuse to participate in the study, they will be sedated with propofol according to the anesthetic standards. The investigator or physician who examines the subject may decide to remove the subject from the study if the subject has an emergency medical problem (allergic reaction or acute health problem).

### Ethical approval

The trial is approved by the Committee on Ethics of Biomedicine Research, Shidong Hospital Affiliated to University of Shanghai for Science and Technology (YPSDKY2020-004-010).

### Allocation and allocation concealment

Patients are allocated to the obstructive jaundice group or the control group based on the TBL values after they sign the informed consent form. Because obstructive jaundice is easy to distinguish from the appearance of skin color, it is difficult to double-blind. However, the anesthesiologist assistant is blind to the grouping or induction method but only records the data through a local area network (LAN) in the next room.

### Intervention

After 8 h of fasting, the patients without premedication will be brought into a quiet operating room where a cannula was inserted into the right internal jugular vein under local anesthesia for infusion of remimazolam and liquid. Radial artery catheterization was placed to measure invasive arterial blood pressure. Heart rate (HR), invasive blood pressure (IBP), electrocardiogram (ECG), end-tidal carbon dioxide (ETCO_2_), and oxyhemoglobin saturation (SpO_2_) are routinely monitored during the whole process of research (Philips HP Viridia24/26 M1205A). Apply the BIS sensor (BIS™XP sensor) as recommended by the manufacturer. The patients are asked to keep their eyes closed and covered with gauze to avoid any interference with sound and light stimulation. The temperature of the room is controlled at 23 °C.

The study is designed to record the remimazolam requirement with BIS of 50 as the endpoint. The patients will be treated with remimazolam at a rate of 6 mg/kg/h by a Graseby 3500 syringe pump (SIMS Graseby Ltd., Herts, UK) until the BIS is ≤ 50 longer than 5 s. The assistant anesthesiologist, who is not aware of the study group, observes the vital signs and BIS values in the next room via the LAN, determines the endpoint of titration, and records the dosage of remimazolam used and the time interval between the start and end of the infusion. Then, the patients will be given 0.4–0.6 μg/kg sufentanil and 0.2 mg/kg cisatracurium, and endotracheal intubation will be performed 3 min later for anesthesia induction. Anesthesia is maintained with sevoflurane (1.5–2.5%) at an appropriate standard for surgical procedures. Hemodynamic data are collected and recorded at relevant points during the peri-intubation period.

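### The mg/kg requirement is compared between non-randomised groups with no adjustment for weight relative to ideal; in a worst case, a 5–10% imbalance shifts the target difference by about a fifth to a half

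*Protocol article*

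**What the plan says.** Under Intervention, the infusion is set by body weight: "The patients will be treated with remimazolam at a rate of 6 mg/kg/h", continued until the BIS endpoint is met. Under Number of patients needed, the previous study's values are also per kilogram: "0.13 ± 0.04 mg/kg (*n* = 6) in the obstructive jaundice group and 0.16 ± 0.04 mg/kg (*n* = 6) in the non-obstructive jaundice group". The endpoint sections speak only of the requirement and give no unit of their own, so mg/kg is the natural reading.

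Four other sections matter:

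- **Exclusion criteria:** patients more than 20% above or below ideal weight are excluded, so each patient's actual weight must be set against an ideal weight at screening.
- **Eligibility:** the jaundiced group has neoplasm of the bile duct or pancreatic head. Controls have chronic cholecystitis or intrahepatic stones.
- **Allocation and allocation concealment:** group membership follows total bilirubin. There is no randomisation.
- **Statistical analysis:** groups are compared by an independent-samples t test or a rank-sum test. A multiple regression relates dosage to TBL, TBA, ALB, AST and ALT. No body-size variable is named for either.

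**The concern.** A per-kg endpoint removes the influence of body size only if the dose needed is proportional to the weight in the denominator. If it follows ideal or lean mass more closely than total mass, a patient who is heavy for their ideal weight shows a lower mg/kg and looks more sensitive. A patient who is light for it looks less sensitive.

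In a randomised trial this would mostly add noise. Here the groups are defined by disease, and nothing in the design balances weight relative to ideal between patients with cancer and patients with gallstone disease or cholecystitis. A systematic imbalance would carry straight into the primary comparison and would not shrink with more patients. It could mask a real increase in sensitivity if the jaundiced patients are relatively lighter, or exaggerate one if they are relatively heavier.

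The recorded infusion time is no independent check. At 6 mg/kg/h, which is 0.1 mg/kg/min, 0.13 and 0.16 mg/kg correspond to 78 s and 96 s. Time is therefore the requirement per programmed kilogram on another scale.

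**Working it through.** **1. The plan's own sample size.** Inputs from Number of patients needed: means 0.13 and 0.16 mg/kg, SD 0.04 in each group, "with *α* = 0.05 and power = 0.8".

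- Effect size = (0.16 − 0.13)/0.04 = 0.75.
- n = 15.7/0.75² + 1 = 27.91 + 1 = 28.91, rounded up to 29 per group. This matches the plan.
- Two-sided t-test power at 29 per group: 0.801.
- 29 × 1.1 = 31.9, so 32 per group, as stated.

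The target difference is 0.03/0.16 = 18.75% of the control mean. Power at 29 evaluable per group is barely above 0.80.

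**2. Worst-case scaling.** Assumptions, neither of which the article states: the requirement per kg of ideal weight is 0.13 (jaundiced) and 0.16 (control), and results are expressed per kg of actual weight. With r the group's mean actual/ideal ratio,

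observed mg/kg = requirement per ideal kg / r.

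Controls are set at r = 1 and the jaundiced group at r = 1 − g (lighter) or 1 + g (heavier). Power is for a two-sided t test with 29 per group and SD 0.04.

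| Gap g | Jaundiced lighter: 0.16 − 0.13/(1 − g) | Share of target | Power | Jaundiced heavier: 0.16 − 0.13/(1 + g) | Share of target |
|---|---|---|---|---|---|
| 3% | 0.0260 | 87% | 0.68 | 0.0338 | 113% |
| 5% | 0.0232 | 77% | 0.58 | 0.0362 | 121% |
| 10% | 0.0156 | 52% | 0.31 | 0.0418 | 139% |
| 15% | 0.0071 | 24% | 0.10 | 0.0470 | 157% |

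**3. No true effect.** Suppose both groups need 0.16 per ideal kg and the jaundiced group is relatively heavier.

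- 5% gap: 0.16 − 0.16/1.05 = 0.0076 mg/kg of spurious difference; rejection probability about 0.11 instead of 0.05.
- 10% gap: 0.16 − 0.16/1.10 = 0.0145 mg/kg; rejection probability about 0.28.

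**4. Partial scaling.** If the total dose rises with actual weight to the power 0.75, the observed mg/kg is multiplied by r^(−0.25).

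- 10% lighter: 0.13 × 0.90^(−0.25) = 0.1335, so the difference is 0.0265, or 88% of target (about 12% lost).
- 5% lighter: 0.13 × 0.95^(−0.25) = 0.1317, so the difference is 0.0283, or 94% of target.

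**5. What erasing or doubling would take, under worst-case scaling.**

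- Erase: 0.13/(1 − g) = 0.16 gives g = 18.75% with controls at ideal weight. Split around ideal, the jaundiced group would be 10.3% below and controls 10.3% above.
- Double to 0.06: 0.13/(1 + g) = 0.10 gives g = 30% with controls at ideal weight, which lies outside the ±20% window. Split around ideal, the jaundiced group would be 10.1% above and controls 10.1% below.

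**The case against.** **The stronger reading.** A reader might note that 20% of 0.16 is 0.032 mg/kg, slightly more than the whole target of 0.03, and infer that a modest body-size difference could erase or double the effect. The documents do not support that. The 20% limit applies to individual patients, whereas the target is a difference in group means. Step 5 shows that erasing or doubling needs a gap of about 19–30% between means. If weights were spread uniformly over the window (an assumption), the SD of the ratio would be 40/√12 = 11.5 points and the standard error of the difference between groups 11.5 × √(2/29) = about 3 points. A gap near 20 points could only be systematic, and nothing in the article suggests one.

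**The scaling is assumed.** The article gives no weight data and no evidence on how the requirement varies with body composition. Step 2 is the extreme case and step 4 shows how far it can shrink. This stands, and neither the size nor the direction of any bias can be settled from the documents.

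**The pilot may already include it.** If the previous study used actual weight, the 0.03 mg/kg is already net of any typical weight difference, and the power loss in step 2 would be counted twice. That is fair as to power. It does not protect interpretation, because part of the observed difference could still reflect body size.

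**It may be in fuller documents.** The weight basis for programming a pump can be left to the full protocol, and its absence from an article is no fault. Nor does anything indicate that the three centres use different bases. Covariates may also be expanded in an analysis plan. The point therefore rests on what the article does state: a two-sample test between groups that were not randomised, and a list of regression covariates without a body-size term.

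**The window helps.** Excluding patients beyond 20% of ideal bounds the distortion. It does not balance the groups within that range.

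**Conclusion.** The point holds in a limited form. Weight relative to ideal is a plausible confounder of a per-kg endpoint in this comparison, and the stated analysis does not address it. If the requirement follows ideal weight entirely and mg/kg uses actual weight, a 5–10% gap between group means removes about 23–48% of the target difference or adds about 21–39%, depending on direction. With an exponent of 0.75, a 10% gap removes about 12%. Both the gap and the scaling are assumptions. The case for acting is that the possible bias is material against a 0.03 mg/kg target with almost no spare power, and the remedy is nearly free. It does not make the mg/kg endpoint wrong.

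**What to change.** Keep the mg/kg endpoint. For the primary comparison, regress the requirement on group with the actual/ideal weight ratio as a covariate, and report the adjusted group difference with its confidence interval. As a sensitivity analysis, report the requirement per kg of actual weight and per kg of ideal weight. The dose used is recorded, and both weights are needed to apply the exclusion criterion, so no new measurement is required.

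State one weight basis for the infusion and the endpoint, the same at all three centres. Which basis to use for dosing is for the sponsor to decide.

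The cost is one derived variable, a sentence or two of text and one degree of freedom. If the groups do differ in the ratio, the adjusted estimate is also somewhat less precise, which is the price of separating the two effects. With a 10-point gap and an assumed within-group SD of 11.5 points, the variance inflation is about 1 + (10/11.5)²/4 = 1.19, or roughly 9% on the standard error before any gain from reduced residual variance.
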